**3.9 Health administrative data**

All participants in the study will have the opportunity to consent to have their data linked with administrative health data held at ICES. Linkage between administrative data holdings at ICES are conducted using a unique identifier for all people eligible for OHIP funded services in the province of Ontario. Data linkage will allow for the use of additional contextual data that can help further identify trajectories as well as real-world outcomes that may occur outside of the context of care at CAMH. For example, hospitalizations at other mental health and medical facilities, ER contacts, contact with primary care physicians, as well as data on mortality and morbidity. All linked data will be deidentified and held and analyzed at ICES. ICES is a prescribed entity under section 45 Ontario's Personal Health Information Privacy Act and all practices and procedures relating to data use are regularly reviewed and approved by the Office of the Information Privacy Commissioner/Ontario.

The proposed data linkage will allow for 1) the evaluation of real world outcomes and services use in cohort participants for a longer duration during a passive follow-up period and 2) comparison to other people with SSDs who may be receiving similar services in the community or have a SSD but are not connected with services. The proposed methodology has recently been used to evaluate the real-world effectiveness of early psychosis intervention services in London, Ontario [(Anderson et al., 2018)](https://www.zotero.org/google-docs/?UFkg3e) and is increasingly being used in other jurisdictions to evaluate real-world outcomes of mental health services where health administrative data are available [(Harris et al., 2019; Mötteli et al., 2018; Stroup et al., 2015; Yu et al., 2009)](https://www.zotero.org/google-docs/?mseosv). Moreover, this methodology and use of health administrative data can contribute to building evidence in settings where randomized trials may not be feasible and can be limited by small sample sizes (which precludes the study of rare events), strict inclusion criteria (which may limit real-world applicability), short duration of follow-up and other ethical considerations.

**3.9.1 Study population and design**

Participants who consent to have their data linked with administrative health data will be eligible to have both historical and future services use linked from the time of cohort entry. Participants who have a OHIP card will be able to consent for direct linkage, and participants who consent but have any uncertainty with their OHIP number will be linked using a deterministic process.

Further use of administrative data will enable comparison of service use and outcome between:

1. Participants that are part of the cohort at CAMH (accessing specialized mental health services at CAMH),
2. People with a SSD who are accessing specialized mental health services in the community (including ACT, ICM and case management services but not at CAMH), and
3. People with a SSD who reside in Toronto but are not currently receiving specialized mental health services

Diagnosis of a SSD in the comparison groups in the health administrative data will be ascertained using a validated algorithm that captures all incident cases of SSD [(Kurdyak et al., 2015)](https://www.zotero.org/google-docs/?SkNgwy). The comparison groups will be restricted to people who reside in areas of Toronto where outpatient services at CAMH are offered and restricted to people who have not received regular outpatient services at CAMH.

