**3.1 Participants**

Participants will be eligible for this study if they: 1) are 16 years of age and older; 2) have a DSM-5 diagnosis of any schizophrenia spectrum disorder (SSD; e.g., schizophrenia, schizoaffective disorder, schizophreniform disorder, brief psychotic disorder, delusional disorder, unspecified schizophrenia spectrum or other psychotic disorder, other specified schizophrenia spectrum and other psychotic disorder, substance/medication-induced psychotic disorder), or related psychotic disorders (including bipolar I disorder with psychotic features or major depressive disorder with psychotic features); and 3) have adequate fluency in English to participate in clinical care without the need for a translator . Of note, participants will be eligible regardless of duration of illness, co-morbid mental or physical health conditions, capacity to consent to treatment, or whether they are receiving inpatient or outpatient services at CAMH. Participants will provide written informed consent, and for those individuals deemed incapable to consent to treatment by their treatment team and have a substitute decision-maker (SDM), their SDM will provide written informed consent in conjunction with participant assent to study participation. These broad eligibility criteria will serve to support generalizability of the sample and maximize the opportunity to evaluate the influence of common co-occurring illnesses on longitudinal outcome trajectories. Caregivers of study participants will also be invited to participate with the consent of the study participant.

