**3.9.4 Outcomes**

The primary outcome will be the number of mental health hospitalization following the cohort entry period. Secondary outcomes will include the number of medical hospitalizations, days spent in hospital (both in mental health and medical beds), ED visits, suicide and self-harm attempts and mortality.

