Recruitment of participants for this study will take place across all outpatient and inpatient clinical services at CAMH where individuals with SSDs may be receiving care, and include both new and existing patients receiving clinical services. Sequential cohorts of participants will be recruited based on duration of illness, enabling an accelerated longitudinal design for this study that will serve to maximize coverage of longitudinal functional trajectories across illness stages. Through regular monitoring of participant recruitment, we will balance recruitment across these multiple cohorts. Core research assessments will mirror measurement-based care assessments and metabolic monitoring being implemented across these clinical services, with sharing of assessment results with the patient’s clinical team. All participants will be offered the opportunity to participate in the neuroimaging and additional laboratory/biological components of this study either as part of this study, or ideally through shared participation in existing complementary studies already taking place in the Division. Harmonization of study assessments and data sharing with existing clinical research studies will enable integration and collaboration across clinical research studies in the Division, maximize recruitment efforts, and leverage existing funded research studies for data collection. With regards to the potential participant pool from which individuals could be recruited, current patient volumes across Schizophrenia Division outpatient clinical services at CAMH, for example, indicate that over 4000 unique patients were seen over the past year, with an average of over 1900 patients seen per month. Based on these volumes, and the integration of study assessments for this proposed work within the context of routine clinical care for such patients within existing clinical services at CAMH, this study will aim to recruit 500 participants per year for 2 years, yielding a total sample of 1000 participants enrolled in this study (i.e., approximately 10 participants per week from over 15 outpatient and inpatient clinical services).

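### The ICES 'CAMH services' group includes cohort members recruited as inpatients, the two comparators are defined by community care or no specialised care, and matching cannot balance that difference against the no-service group

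*Protocol*

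**What the plan says.** **Who enters the cohort.** Protocol section 3.1 makes people eligible regardless of "whether they are receiving inpatient or outpatient services at CAMH". Section 5.0 (Recruitment and Sampling) states: "Recruitment of participants for this study will take place across all outpatient and inpatient clinical services at CAMH". It plans "approximately 10 participants per week from over 15 outpatient and inpatient clinical services" and does not say what share will be enrolled from wards.

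**How the ICES groups are formed.** Section 3.9 describes a "comparison to other people with SSDs who may be receiving similar services in the community", or with people not connected to services. In 3.9.1, group 1 is "Participants that are part of the cohort at CAMH (accessing specialized mental health services at CAMH"). Group 2 is people using specialised services in the community, with ACT, ICM and case management as examples, and not at CAMH. Group 3 is "People with a SSD who reside in Toronto but are not currently receiving specialized mental health services". Both comparators are further "restricted to people who have not received regular outpatient services at CAMH". Section 3.9.2 matches linked cohort members 1:1:1 on a propensity score and calls the three exposures CAMH services, community services, and eligible but no service.

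**What is counted.** In 3.9.4 the primary outcome is the number of mental health hospitalisations after the cohort entry period. Secondary outcomes include "days spent in hospital (both in mental health and medical beds"). Section 3.9.6 compares costs between the groups, including the cost of all hospitalisations.

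**What is adjusted for.** The covariates named in 3.9.5 include neither inpatient status at entry nor previous psychiatric admission.

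**The concern.** Being in a psychiatric bed at time zero is closely tied to the outcomes being counted: admissions, bed-days and hospital cost. Group 1 admits people in that state. The comparator definitions either describe community care or appear to rule the state out.

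There are two consequences. Ward-recruited members bring their post-discharge readmission risk into the primary count. Any days left in the admission during which they enrolled can enter bed-days and cost. Both would be attributed to CAMH services even if those services had no effect, which could make CAMH look worse than it is or hide a real benefit. An inpatient ward is also not the kind of service that section 3.9 sets out to compare with community care.

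**Working it through.** The protocol gives no sample size, event rate or effect size for the ICES comparison, so there is no stated figure to reproduce. The check has two parts.

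**1. The definitions side by side**

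| | In a psychiatric bed at time zero? | Source |
|---|---|---|
| Group 1 | Yes, for those recruited on a ward | 3.1, 3.9.1, 5.0 |
| Group 2 | Not part of the definition; not expressly barred | 3.9.1 |
| Group 3 | Excluded on the ordinary reading of its definition | 3.9.1 |

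Leaving inpatient status out of the propensity score, as the list in 3.9.5 does, leaves the imbalance in place. Putting it in does not solve the problem for group 3: if that group contains no inpatients, a ward-recruited member has no match on this variable. This is a lack of overlap created by the group definitions.

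**2. Size under no service effect (every input is an assumption)**

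- f = share of group 1 in hospital at entry
- g = share of comparators in hospital at index
- L = mean days remaining in the entry admission
- k = later admission rate in people who were inpatients at entry, relative to others

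Excess days per group 1 member = (f − g) × L. With g = 0:

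| f | L = 14 | L = 30 | L = 60 |
|---|---|---|---|
| 5% | 0.7 | 1.5 | 3.0 |
| 10% | 1.4 | 3.0 | 6.0 |
| 20% | 2.8 | 6.0 | 12.0 |
| 30% | 4.2 | 9.0 | 18.0 |

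These days count only if bed-days and cost are measured from entry.

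Spurious rate ratio for later admissions = [1 + f(k − 1)] / [1 + g(k − 1)]. With g = 0:

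| f | k = 1.5 | k = 2 | k = 3 |
|---|---|---|---|
| 5% | 1.025 | 1.05 | 1.10 |
| 10% | 1.05 | 1.10 | 1.20 |
| 20% | 1.10 | 1.20 | 1.40 |
| 30% | 1.15 | 1.30 | 1.60 |

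*Some comparators also in hospital.* With f = 20% and g = 5%, the ratio is 1.10/1.025 = 1.07 at k = 1.5 and 1.40/1.10 = 1.27 at k = 3. Excess days are 0.15 × 14 = 2.1 to 0.15 × 60 = 9.0. With f = g, the ratio is 1.00 and the excess is 0.

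*Chance of a false positive.* This takes a two-sided 5% Wald test on the log rate ratio, negative binomial counts, comparator mean 0.3 admissions and dispersion 1. The standard error is √[(1/m₀ + 1)/n + (1/m₁ + 1)/n]. For f = 20%, k = 2 and n = 500 per group, m₁ = 0.36, SE = √[(4.333 + 3.778)/500] = 0.127, and ln 1.20 / 0.127 = 1.43. The rejection probability is 0.30.

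| f, k | n = 500 per group | n = 1000 per group |
|---|---|---|
| 5%, 1.5 | 0.05 | 0.06 |
| 10%, 2 | 0.11 | 0.18 |
| 20%, 2 | 0.30 | 0.53 |
| 20%, 3 | 0.77 | 0.97 |

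**The case against.** **The entry admission and the primary outcome.** A reader might infer that the open admission itself inflates the primary count. The text does not support that. Section 3.9.4 counts hospitalisations following entry, and an admission already under way is not plainly one of those. It gives no start date for the secondary outcomes either. The primary outcome is therefore affected mainly through later readmissions, and the entry admission matters for bed-days and cost. This objection stands and limits the point.

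**Whether the burden falls almost wholly on CAMH.** That too might be inferred, but it is not established. Nothing stops a group 2 client from being in a non-CAMH bed at the match date, and 3.9.1 does not define specialised services closely enough to settle every group 3 case. Such people dilute the imbalance. They remove it only if they are as common as inpatients in group 1.

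**Covariates can be added.** Section 3.9.2 commits to a score using all covariates that affect assignment and outcome, and admission history is available in the linked data. Adding prior admissions is consistent with the plan and would help. It does not supply group 3 members who are inpatients at time zero.

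**Detail for the analysis plan.** A comparator index date and a rule for open admissions are ordinary analysis-plan matters, and their absence is not the point. The group definitions are fixed in the protocol.

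**Barring comparators with CAMH inpatient care.** The comparator restriction mentions only CAMH outpatient care, so extending it to inpatient care may look like the natural repair. It would do harm. Applied at baseline, it makes comparators selectively less prone to admission while group 1 keeps such people. Applied during follow-up, it selects on the outcome.

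**Scope.** The ICES comparison is not in the stated objectives or the power analysis. That is correct and limits the consequence.

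**Conclusion.** The point holds for the ICES service comparison. As defined, some people in hospital at time zero are compared with groups that by definition largely are not, and matching cannot balance this against group 3. The expected direction, if people recently in hospital are readmitted more often, is against CAMH: in the primary hospitalisation count through readmissions, and in bed-days and cost also through any remaining entry-admission days.

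The size cannot be determined, because the protocol gives no inpatient share, remaining stay or readmission ratio. At 5% inpatients and 1.5-fold readmission the bias is small (rate ratio 1.025). At 20% and two- to threefold readmission it is 1.20 to 1.40 with no inpatient comparators. The co-primary trajectory outcomes (RAS, WHO-DAS, PSP) are not touched. It should be corrected before matching.

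**What to change.** In sections 3.9.1, 3.9.4 and 3.9.5:

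1. Restrict the main three-way comparison to cohort members not in hospital at cohort entry, and to comparators not in hospital on the matched index date.
2. Exclude any admission open on the index date from the hospitalisation count, bed-days and cost, in all groups.
3. Name prior psychiatric admissions among the propensity covariates. This also addresses members who were discharged shortly before entry.
4. Analyse inpatient-recruited members in a secondary two-group comparison, starting at discharge, against people discharged from non-CAMH psychiatric beds in the same period.

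The change is one of wording. The hospital holdings, including OMHRS, are already among the data sources in 3.9.3. The cost is a smaller group 1 in the main comparison, whose result then applies to people not in hospital at entry. Reporting the number enrolled as inpatients would show how much was at stake.

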**3.2 Procedures**

Recruitment and Informed Consent:

At the initial baseline visit, participants and their SDM where applicable, will be provided detailed study information via the informed consent form, and through discussion with the study team. The informed consent process will take place in person or through Cisco Webex video conferencing and REDCap as described in CAMH SOP #HSR 229: e-Consent Framework. Study staff will assess eligibility via the inclusion/exclusion criteria following obtaining consent. No study procedures will be completed prior to obtaining informed consent.

Participants will be recruited through the Schizophrenia Division Central Recruitment Model (REB #036/2020), the CAMH Research Registry, physician/clinician referrals, and through direct contact with former research participants who participated in previous studies of the Principal Investigators and Co-Investigators of this study who consented to be contacted for future research studies. If a patient is interested to learn more about the study, the physician/clinician may pass the patient’s preferred contact information to a research staff for follow up. A study recruitment flyer will be shared with participants who need more information about the study. This flyer will also be posted on bulletin boards across CAMH. Study information will also be available to participants through the CAMH Research Connect website.

The Schizophrenia Division Centralized Recruitment Procedure will be used to recruit participants for this study. The Centralized Research Personnel will prescreen patients for eligibility to participate using minimal inclusion/exclusion criteria outlined in REB #036/2020. Once a patient has been identified, the Centralized Research Personnel will send preferred contact information to the Study Specific Research personnel who will reach out to the patient to further explain the study. No information will be passed to the Study Specific Research Personnel prior to the patient’s verbal consent.

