**3.9.2 Propensity score matching**

Propensity score matching is proposed to identify people that will be comparable to the cohort participants. By definition, a propensity score is the probability of treatment assignment conditional on observed baseline covariates. Therefore, among people with the same propensity score, the distribution of observed baseline covariates will be the same between treated and untreated groups. An estimated propensity score can be obtained by regressing treatment status on observed baseline covariates. To reduce observed confounding participants can be matched based on the propensity score. Estimated treatment effects can then be obtained by directly comparing outcomes between matched groups using appropriate methods for matched samples. Propensity score matching mimics some aspects of randomization of a traditional trial but uses observational data. However, unlike a randomized trial, propensity score matching can only account for measurable confounding and not unmeasurable confounding.

For the purpose of this study a propensity score will be calculated based on all covariates that can impact treatment assignment and outcomes. Linked cohort participants will be matched to people in the health administrative data based on 1:1:1 ratio, without replacement, on the propensity score to ascertain two additional exposure groups. This will enable the comparison of three exposures (CAMH services, community services, eligible but no service).

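### In the ICES matched comparison, both comparison groups must live in CAMH-served areas of Toronto, but the CAMH group has no residence rule and no stated condition of current CAMH care

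*Protocol*

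**What the plan says.** Protocol section 3.9.1 defines three groups. Group 1 is "Participants that are part of the cohort at CAMH (accessing specialized mental health services at CAMH". Group 2 uses specialized services in the community but not at CAMH. Group 3 lives in Toronto and uses no specialized service. The section then adds: "The comparison groups will be restricted to people who reside in areas of Toronto where outpatient services at CAMH are offered". Both comparison groups must also be without regular CAMH outpatient care.

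Section 3.9.2 gives the matching rule: "Linked cohort participants will be matched to people in the health administrative data based on 1:1:1 ratio, without replacement, on the propensity score". It names no subset of the linked participants. Section 3.9 says that linkage rests on "a unique identifier for all people eligible for OHIP funded services in the province of Ontario".

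On who can be in the cohort, the three numbered criteria in section 3.1 are age, diagnosis and fluency in English. The section then lists things that do not affect eligibility, ending "or whether they are receiving inpatient or outpatient services at CAMH". Section 3.2 recruits by clinician referral and central screening, but also from the CAMH Research Registry and "through direct contact with former research participants who participated in previous studies". Section 5.0, under Recruitment and Sampling, says "Recruitment of participants for this study will take place across all outpatient and inpatient clinical services at CAMH", and that these "include both new and existing patients receiving clinical services".

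The outcomes in section 3.9.4 are led by the count of mental health hospitalizations after cohort entry. The covariates in section 3.9.5 include area marginalization, with neighbourhood noted only as something to consider.

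**The concern.** The comparison is meant to contrast three kinds of care: CAMH, other specialized community care, and none. For that, the groups should be drawn from the same source population and differ in the care received. As written, two groups come from a defined set of Toronto areas and the third may come from anywhere in Ontario.

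The primary outcome makes this matter. How often a person is admitted to a psychiatric bed plausibly depends on local bed supply, emergency services and community programmes as well as on clinical state. A cohort member from another part of the province, matched to a resident of a CAMH-served area, brings that local difference into the contrast, where it would be read as an effect of CAMH services. The cost comparison between groups in section 3.9.6 would carry the same difference.

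A second, smaller issue is that group 1 is labelled by its use of CAMH services while membership is decided by cohort enrolment. If someone enrols without being in CAMH care, the label and the membership part company.

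**Working it through.** The protocol gives no sample size, power or event rate for the ICES comparison, so there is no figure to reproduce. The check is to set the selection rules side by side.

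1. **Residence.** Groups 2 and 3 are confined to the CAMH-served Toronto areas (3.9.1). For group 1, section 3.9.1 gives no residence condition, section 3.9.2 takes the linked participants as a whole, section 3.1 has no geographic criterion, and section 3.9 requires only provincial coverage. The rule applies to two groups of three.

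2. **Whether the propensity score repairs it.** There are two cases.
   - Location is not in the score. Area marginalization describes how deprived an area is, not where it is or what services it has. An out-of-area participant is then matched to an in-area person from a similarly marginalized neighbourhood, and the difference in local supply remains.
   - Location is in the score, as section 3.9.2 would imply if location affects both assignment and outcome. Everyone in the pooled data who lives outside the restricted areas is then in group 1 with certainty, because the protocol has removed all such people from groups 2 and 3. Their probability of being in group 1 is 1, and no comparator from their area exists. This lack of overlap comes from the population rule, and adding covariates cannot cure it.

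3. **Current CAMH care.** Sections 3.9.1 and 5.0 both describe the cohort as people receiving CAMH services. The wording in section 3.1 is ambiguous: it can be read as presupposing CAMH care or as waiving it. The Research Registry and former-participant routes in section 3.2 carry no requirement of current care. Care is therefore described, but nothing makes it a condition of entering the matched comparison.

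4. **Size.** Let q be the share of matched group 1 members living outside the areas, and d the average difference in hospitalization count that is due to location alone. The mean difference between group 1 and a comparison group is then shifted by q × d. The protocol gives neither q nor d, nor the sign of d. The shift is zero if either is zero.

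**The case against.** The strongest reply is that the cohort is, in practice, a CAMH patient cohort. Section 3.9.1 calls group 1 users of CAMH specialized services, and section 5.0 places recruitment in CAMH clinical services. That stands. A reader might infer from the numbered criteria that group 1 could consist largely of people out of care, and the documents do not support that. Only the registry and former-participant routes leave the gap, and no numbers are given for them.

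Two other inferences also fail. Barring regular CAMH outpatients from the comparison groups might look like a further selection imbalance, but it defines the exposure contrast. Enrolled inpatients without CAMH outpatient follow-up might look misclassified, but the exposure is CAMH services, not outpatient services, and the protocol enrols inpatients deliberately.

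It can also be said that section 3.9.2 intends to use every relevant covariate, that it acknowledges unmeasured confounding, and that handling of non-overlap may be left to an analysis plan. This is fair as regards modelling detail. It does not reach the residence point, because the protocol itself fixes the population rule and fixes it unevenly.

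Finally, this comparison is not among the stated objectives or hypotheses and does not touch the three co-primary trajectory outcomes. That limits the weight of the point.

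**Conclusion.** The residence mismatch is confirmed on the text, and the planned matching does not remove it. The point about CAMH care holds only in the narrower sense that such care is described for group 1 and not required for the matched comparison.

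The size of either effect cannot be computed from the protocol. A reader might want to express the second as a dilution in proportion to the share of group 1 not in CAMH care. That would require those members to have the same hospitalization risk as the comparison groups. The protocol gives no support for this, and the two comparison groups need not share one risk.

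The conclusion assumes that some linked participants live outside the restricted areas and that local supply affects admissions. Both are plausible and neither is quantified. This is an inexpensive improvement to a secondary part of the study. It does not threaten the main objectives.

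**What to change.** In sections 3.9.1 and 3.9.2, limit the linked participants used in the three-way matched comparison to those who:

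- live, at cohort entry, in the same CAMH-served Toronto areas that define the comparison groups; and
- receive CAMH specialized services, inpatient or outpatient, at or before cohort entry, within a look-back period stated in the protocol.

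Both conditions should use only information available at entry. A window running past entry would select group 1 on later care and survival and introduce a new bias. An outpatient-only rule would drop inpatients whom the design means to include. All other linked participants stay in the descriptive and within-cohort trajectory analyses.

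The data are already planned: postal code at baseline (section 3.8 and Appendix 1) and treatment encounters from the medical record (section 3.10). The cost is a few sentences of protocol text, a filter, and a somewhat smaller matched CAMH group.

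The alternative is to lift the residence restriction on the comparison groups and match on geography. That would also mean redefining group 3, which is itself limited to Toronto residents.
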